### Measures of feasibility

Full-scale trial feasibility will be assessed by recruitment rate (and reasons for non-participation) and attrition rate, adherence to the protocol and safety of the intervention. Adherence to the prehabilitation protocol will be monitored through the kinesiologist's logbook. For every participant, date of encounter and exercises

[figure not shown]

**Fig. 1** Progression of squat exercise

**Table 1** Schedule of interventions and outcome measures

| Time point                                 | Location          | Data collection                                      |
|--------------------------------------------|-------------------|------------------------------------------------------|
| Baseline assessment                        | In clinic (UQTR)  | Questionnaires a
Physical measurements |
| 6 weeks prehabilitation                    | In clinic (UQTR)  | Physical fitness evolution                           |
| Post-intervention, Preoperative assessment | In clinic (UQTR)  | Questionnaires
Physical measurements              |
| Surgery                                    | Hospital (CSSSTR) | Perioperative data b                      |
| 6-week follow-up                           | In clinic (UQTR)  | Questionnaires
Physical measurements              |
| 3-month follow-up                          | Mailing           | Questionnaires c                          |
| 6-month follow-up                          | Mailing           | Questionnaires c                          |

aQuestionnaires include NRS, ODI, EQ-5D-3 L, Tampa Scale of Kinesiophobia, and BDI

bPerioperative data refers to blood loss, length of surgery and intraoperative complications

cIn addition to the regular questionnaire packet, a home-made questionnaire regarding physical activities undertaken during the postoperative phase will be mailed to the participants

BDI Beck Disability Index, CSSSTR Centre de Santé et de Services Sociaux de Trois-Rivières, EQ-5D-3 L EuroQol-5D-3 L, ODI Oswestry Disability Index, NRS Numerical Rating Scale, UQTR Université du Québec à Trois-Rivières

performed (including, number of repetitions and levels of difficulty, perceived effort and discomfort – location, intensity and character) will be recorded. Exercises have been specifically designed as to not aggravate stenotic symptoms (slight lumbar flexion is preserved) while performing them. However, in case of unusual or worsening discomfort, the chiropractor will re-evaluate the participant to ensure that there are no safety issues or possible threats to the participant. If we encounter a number of problems with a given exercise, even with its easiest version, the specific exercise will be considered irrelevant for the population under investigation and the research team will discuss how to come up with an alternative that targets the same objective.

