### Hospital preoperative management

Patients undergoing surgical intervention at the regional hospital do not receive any particular physical intervention (exercises, manual therapy, etc.). On their last encounter before the day of surgery they are given a

pamphlet summarizing tips on how to keep a good back posture when getting in or out of bed and when sitting down. All participants will be questioned on the amount and type of physical activity performed weekly, if any, regardless of their group allocation.

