### Primary outcome measures

#### Back and leg pain

Pain intensity will be assessed using an 11-point NRS. Each patient will subjectively rate their current level of leg and back pain on a scale of 0 to 10 (0 being an absence of pain 10 being the worst pain imaginable) [21].

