### **Discussion**

Despite the development of innovative surgical approaches and efforts being made to optimized treatment plans for the management of low back pain, the role of exercise therapy as an adjunct to operative modalities remains unclear. This pilot study will provide preliminary data that will be used as a 'stepping stone' for a future large-scale clinical study investigating the effects of a prehabilitation program on patients' recovery following spinal stenosis surgery. In addition to the assessment of possible effects and associations that may be worth investigating in a subsequent larger trial, the study will allow for documentation of patient compliance and

satisfaction regarding a prehabilitation protocol based on exercise training.

In a broader perspective, the observations gathered during the pilot study will expand the knowledge related to the functional changes affecting patients after lumbar surgery, allowing for identification of specific components of physical fitness that should be targeted in future prehabilitation protocols. Similarly, it is believed that the results of this study could eventually lead to improvement in the delivery of spinal care. Identification of patients' characteristics likely to respond favorably to prehabilitation will help target the individuals for whom it should be considered to limit symptoms persistence, and post-surgery complications and side-effects.

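### Safety is a feasibility measure, but no adverse-event collection applies alike to both arms, so discrete events before and after surgery cannot be compared

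*Protocol*

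**What the plan says.** The Measures of feasibility section of the protocol names four things by which feasibility of a full trial will be judged: recruitment, attrition, "adherence to the protocol and safety of the intervention". Safety is given no definition, event list or grading.

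The procedures that follow in that section all belong to the training sessions:

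- "Adherence to the prehabilitation protocol will be monitored through the kinesiologist's logbook". At each encounter the exercises performed are noted, and "perceived effort and discomfort – location, intensity and character) will be recorded".
- "in case of unusual or worsening discomfort, the chiropractor will re-evaluate the participant", to check that there is no safety problem. The text does not say that the result is recorded as an event.

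Table 1 schedules perioperative data at surgery. Its note b states: "Perioperative data refers to blood loss, length of surgery and intraoperative complications". The later rows of the table list questionnaires and, at 6 weeks, physical measurements. No row lists complications after surgery.

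The Hospital preoperative management section describes a pamphlet for controls and no training. The Ethical considerations section reserves the right to stop the trial over adverse-event risk or worsening symptoms, without saying how such information is gathered.

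**The concern.** If the plan is followed to the letter, the only record before surgery that resembles event reporting exists in one arm. Trained patients are seen and asked about discomfort up to 3 x 6 = 18 times. Controls are seen at baseline and again at the preoperative assessment. A fall, a new deficit or an unplanned visit to a doctor is far more likely to come to the team's notice in the trained arm. After surgery neither arm has any listed source for infection, readmission or reoperation.

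At stake is the pilot's statement on safety, which is meant to inform the decision on a full-scale trial, and any judgement made under the stopping statement. Unequal ascertainment can make the programme look worse than it is. Missing postoperative events can make it look safer than it is. The randomised control group is there to separate these, but for discrete events the plan does not use it. The fault lies in what is collected, so it belongs to the protocol and cannot be left to an analysis plan.

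**Working it through.** The plan states no figure on safety, so there is nothing to reproduce. The check has two parts.

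**1. What is collected, by period and arm**

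| Period | Trained arm | Control arm | Comparable by arm? |
|---|---|---|---|
| Wait: session discomfort | Logbook, up to 18 entries | None (no sessions) | No |
| Wait: symptom change | NRS, ODI, CGI-I, medication journal | Same | Yes |
| Wait: falls, new deficit, unplanned care | Not listed | Not listed | No |
| Operation: blood loss, duration, complications | Listed | Listed | Yes |
| After surgery: symptom change | NRS and ODI at 6 weeks, 3 and 6 months; medication journal | Same | Yes |
| After surgery: complications, readmission, reoperation | Not listed | Not listed | No |

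The sources are Measures of feasibility and Table 1, Data collection, the outcome sections on pain, disability, pain medication and global impression of change, and Hospital preoperative management.

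The rows marked Yes cannot stand in for those marked No:

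- The pain scale asks about the present: "Each patient will subjectively rate their current level of leg and back pain on a scale of 0 to 10". A flare that settles before the visit leaves no trace.
- The CGI-I gives one net rating for the six weeks and is used at the preoperative assessment only.
- The journal counts pills, not events.
- The neurological examination is described under the baseline assessment (Additional measurements), and no repeat is stated. Strength and walking tests are repeated preoperatively and at 6 weeks, but they cover only part of what a new deficit would show.

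**2. What equal collection could deliver at this size**

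Inputs: 40 patients in two arms (Abstract). The allocation ratio is not stated, so 20 per arm is an assumption.

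Exact two-sided 95 % upper limit when no event is seen among n patients: 1 − 0.025^(1/n).

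- n = 20: 16.8 %
- n = 15: 21.8 %
- n = 10: 30.8 %

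Power of a two-sided 5 % comparison with 20 per arm, for event rates that are assumptions because the protocol gives none:

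- 5 % versus 10 %: about 9 %
- 5 % versus 20 %: about 29 %
- 10 % versus 30 %: about 35 %
- 5 % versus 30 %: about 55 %

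As an illustration, suppose 1/20 and 4/20 were observed. The difference is 15 percentage points. Its standard error is √(0.05 × 0.95/20 + 0.20 × 0.80/20) = 0.102, and 1.96 × 0.102 = 0.20. The approximate 95 % interval runs from −5 to +35 points.

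The pilot could therefore describe adverse events by arm but could not test them.

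**The case against.** The strongest reply is that the trial already measures worsening in both arms. Controls are assessed at the same preoperative point. The CGI-I covers exactly the six waiting weeks and runs down to the worst category of deterioration. Pain, disability and analgesic use are recorded in both groups, and both undergo the operation at which complications are noted. All of this stands. A reader might infer that harm cannot be compared with controls at all, or that reports of worsening come from the trained arm only. The documents do not support that reading: symptom worsening and intraoperative complications are comparable by arm.

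The second reply is that the logbook is introduced for adherence, and that its discomfort entries help decide whether an exercise suits this population. That is a tolerability question with no control counterpart, so a one-arm session log is not itself a fault. This also stands.

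Third, a reader might take the Discussion's mention of complications after surgery as a promised endpoint left unmeasured. It is a hope for later use in selected patients and sets no endpoint, so the point does not rest on it.

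Fourth, the numbers are too small for a safety comparison to settle anything. That is correct, and it limits the benefit of the change. The upper limit for zero events in 20 is the same with or without it. Small numbers do not justify unequal collection, however: a descriptive count by arm is informative only if both arms were asked the same thing.

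What none of these replies answers is that discrete adverse events, before and after surgery, have no common means of collection.

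**Conclusion.** The point holds in this limited form. Safety is one of four named feasibility measures, but no adverse-event definition or question applies alike to both arms. Session discomfort is logged in the trained arm only. Complications are recorded only during the operation. Postoperative complications, readmission, reoperation and unplanned care are listed for neither arm. Discrete events outside the operating room therefore cannot be compared, while symptom worsening and intraoperative complications can.

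No event rate is claimed, because the protocol gives none, and the conclusion does not depend on one. The precision figures rest on equal allocation of 40 patients with none lost. They show that the remedy yields description, not a test. This is a cheap improvement that should be made. It is not a flaw that undermines the trial.

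**What to change.** Define an adverse event for this trial and put the same short question to both arms at four existing contacts: the preoperative visit, the 6-week visit, and the 3- and 6-month mailings. It should cover new or worse leg or back symptoms, new weakness, and unplanned care, and after surgery also readmission and reoperation.

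Take postoperative complications from the hospital chart, which the Pain medication section already has the team read for the hospital stay. Events after discharge would rest on the patient's answer, or on reopening the chart at the end of follow-up.

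Report the number of patients with an event by arm, with exact intervals and no significance test, next to worsening on the CGI-I, NRS and ODI. Keep the session logbook as a separate tolerability record for the trained arm, and do not add its entries to the between-arm count.

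The cost is one short form, a few chart fields and slightly longer questionnaires. No visit is added, and no treatment procedure changes.

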### Primary outcome measures

#### Back and leg pain

Pain intensity will be assessed using an 11-point NRS. Each patient will subjectively rate their current level of leg and back pain on a scale of 0 to 10 (0 being an absence of pain 10 being the worst pain imaginable) [21].

#### Back disability

Disability related to back pain will be measured via the validated French version of the ODI questionnaire (version 2.1a) [22]. The ODI contains ten questions related to daily activities, including pain intensity, personal care, lifting, walking, sitting, standing, sleeping, sexual life, social life, and traveling. Each question is rated on a

scale of 0 to 5 points with a maximum of 50. Higher scores indicate greater disability.

### Secondary outcome measures

#### Pain medication

The use of pain medication will be evaluated as the number of pills taken in a day using the patient's hospital chart for the hospital stay period and via a daily self-reported journal for the preoperative and postoperative at-home period.

#### Quality of life

The quality of life will be measured using the EuroQol-5D-3 L questionnaire (EQ-5D-3 L). The EQ-5D-3 L comprises the following 5 dimensions: mobility, self-care, usual activities, pain/discomfort and anxiety/depression. Each dimension has three levels: no problems, some problems, extreme problems. Scores obtained on the EQ-5D-3 L should not be considered as a cardinal score but as an index of perceived health-related quality of life [23].

#### Global impression of change

The patient's global impression of change will be measured using the Clinical Global Impression - Improvement scale (CGI-I). The 7-point scale ranging from 1: very much improved to 7: very much worse, will be used to evaluate patient's perception of change in his or her condition over the preoperative 6-week period. Global impression of change will be measured at the preoperative assessment only and will help evaluate the prehabilitation program effects.

#### Lumbar extensor muscles endurance

Trunk muscle endurance assessment will be done with a modified version of the Sorenson test using an inclined bench. Participants will be positioned on a 30° Roman chair, the iliac crest aligned with the chair's border, the upper body maintained in a horizontal position (parallel to the floor) and the arms crossed on the chest. The test will be stopped when the participant is no longer able to maintain a proper horizontal position (as evaluated by the researcher), becomes too fatigued to continue, or experiences pain.

#### Maximum voluntary contraction

Strength of knee extensor muscles will be assessed using a load cell (Model LSB350; Futek Advanced Sensor Technology Inc., Irvine, CA, USA). Strength of lumbar flexor and extensor muscles will be assessed using an isokinetic testing device (LIDO, Loredan Biomedical Inc., Davis, CA, USA). Each measurement will be taken three times and the mean value will be used for subsequent analyses.

### **Lumbar ranges of motion**

Active lumbar ranges of motion will be assessed with an inclinometer (Digital Dualer IQ Pro™ Digital Inclinometer, Model CM101; JTECH Medical, Midvale, UT, USA). Each range of movement will be measured twice and the mean value will be used for analysis.

### **Walking abilities**

Walking abilities will be assessed using two components of the exercise treadmill examination (time to first symptoms (TFS) and total ambulation time (TAT)). Both variables will be measured at a walking speed of 1.2 mph, on a 4 ° inclined ramp. If ever a participant is unable to keep up with the predetermined walking speed, the examination will be performed using the participant's preferred walking speed. The examination will be stopped at the onset of severe symptoms, defined as the level of discomfort that would cause the patient to stop walking in usual life situations. Walking abilities will serve as an indicator of surgical success.

### **Maximal aerobic capacity**

The maximal aerobic capacity will be estimated based on the results obtained during a submaximal aerobic test and using a linear extrapolation method. The submaximal aerobic test is performed with a Monark ergocycle (Ergomedic 828-E Test Bike, Monark, Varberg, Sweden) and consists of a 3-minute warm-up with an initial workload (from 0.25 kp to 0.5 kp) successively followed by 3-minute periods with progressively increasing workloads until an 85 % maximal heart rate is reached. Time to 85 % maximal heart rate will be recorded.

### **Additional measurements**

Participants will complete a series of questionnaires and clinical examination procedures during the baseline assessment, allowing for exploratory analysis of any baseline features that might be predictors of intervention response. The questionnaires will include the following: demographics including age, gender, months lived with pain, presence of comorbidities and conservative interventions received so far. The Tampa Scale of Kinesiophobia will be used at every time assessment point to evaluate fear of movement and of re-injury because it has been found to be associated with poor performance on a number of physical tests and high scores have proven to be a powerful predictor of postoperative disability. The Beck Disability Index (BDI) will be used at every assessment time point as a screening tool for possible signs of high levels of anxiety and depression. The Minnesota Satisfaction Questionnaire (MSQ) will be used during the baseline

evaluation only in order to assess participant's satisfaction related to work conditions for those employed or on sick leave at the time of the study. Clinical examination will include weight and height measurements and a neurological exam of lower extremity deep tendon reflexes, assessment of fine touch and pinprick sensation, manual muscle testing for strength, ankle clonus and the Babinski test. In addition, participants from both groups will be asked about nature, length and frequency of any physical activities undertaken during the preoperative (assessed orally at the preoperative encounter) and postoperative periods (mailed questionnaire at 3-month and 6-month follow-up).

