### Randomization

Treatment allocation will be made based on randomization and minimization methods. Minimization criteria have been decided based on factors identified by the neurosurgeons known to delay postoperative recovery and include presence of diabetes, objective motor deficits in the lower limbs (confirmed by electromyography), self-reported severe disability (ODI score  $\geq 41$  %) and smoking habit. Patients will be randomized following a computer-generated list of random numbers. An independent research assistant blinded to patient assignment will sequentially number the envelopes containing intervention assignments according to the computer-generated randomization. Opaque and sealed envelopes will be opened in front of the participants at the end of the initial assessment visit.

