### **Statistical analysis**

Participants' characteristics will be summarized using descriptive statistics (mean, standard deviation). The equivalence of groups at baseline in terms of demographic and clinical variables will be assessed using independent samples *t* tests for continuous variables and chi-square tests for categorical variables. Following an intention-to-treat principle, estimates of efficacy (Group and Time main effect, as well as Group x Time interactions) will be analyzed using a repeated-measure analysis of variance (ANOVA). The statistical significance level will be set at 5 % and missing data will be analyzed using multiple imputation methods.

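### The protocol calls baseline Tampa kinesiophobia a strong predictor of disability after surgery, yet neither minimizes on it nor adjusts the ODI analysis for it; this forgoes some precision and leaves chance imbalance uncorrected.

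*Protocol*

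**What the plan says.** - **Prognostic claim.** The Additional measurements section of the protocol says of the Tampa scale that "high scores have proven to be a powerful predictor of postoperative disability". The Design section makes disability, measured by the ODI, one of the two primary outcomes.
- **Timing.** "The Tampa Scale of Kinesiophobia will be used at every time assessment point", and footnote a of Table 1 lists it in the baseline questionnaires. According to the Recruitment and Randomization sections, the envelope is opened at the end of the baseline visit, so the baseline score is taken before allocation.
- **Allocation.** The minimization criteria rest on "factors identified by the neurosurgeons known to delay postoperative recovery". They are diabetes, lower-limb motor deficit, an ODI score of 41 % or more, and smoking. Tampa is not among them.
- **Analysis.** The Statistical analysis section fixes "estimates of efficacy (Group and Time main effect, as well as Group x Time interactions" in a repeated-measures ANOVA at the 5 % level. No covariate is named. The arms are compared at baseline by t tests and chi-square tests, and no consequence of those tests is stated.
- **Use of baseline data.** The stated purpose of the additional baseline measures is exploratory: "allowing for exploratory analysis of any baseline features that might be predictors of intervention response".

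**The concern.** By the protocol's own account, a strong predictor of a primary outcome is known for every patient before allocation, yet neither the allocation nor the stated model uses it. With 40 patients, the variation that Tampa explains stays in the error term of the ODI comparison. If the arms differ on Tampa by chance, the planned analysis does not correct for it.

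The sample size was set by time constraints, the surgery rate at the site and a pilot rule of thumb. More patients are therefore not on offer, and any added precision has to come from the analysis. At stake are the width of the interval for the ODI effect and how far that estimate can be relied on when the larger trial is planned.

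**Working it through.** The plan states no effect size, SD, power or Tampa–ODI correlation, so there is no figure to reproduce.

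**Inputs**
- From the protocol: 40 patients in two arms. I take n = 20 per arm; the allocation ratio is not stated.
- Assumed: a partial correlation r between baseline Tampa and postoperative ODI, given baseline ODI, of 0.2 to 0.5.

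**1. Precision gained by adjusting**

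The residual variance is multiplied by (1 − r²). Estimating the covariate costs a factor of about 1 + 1/(2n − 4) = 1 + 1/36 = 1.028. The net factor is f = (1 − r²) × 1.028, and the gain in equivalent patients is 1/f − 1.

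| r | 1 − r² | f | Net gain in patients | SE ratio √f |
|---|---|---|---|---|
| 0.2 | 0.96 | 0.987 | about 1 % | 0.993 |
| 0.3 | 0.91 | 0.935 | about 7 % | 0.967 |
| 0.4 | 0.84 | 0.863 | about 16 % | 0.929 |
| 0.5 | 0.75 | 0.771 | about 30 % | 0.878 |

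If the estimation cost is ignored, 1/(1 − r²) − 1 gives 4 %, 10 % and 33 % at r = 0.2, 0.3 and 0.5, which is too generous.

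**2. How much baseline ODI already captures**

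Let ρ be the correlation of baseline with follow-up ODI, m that of Tampa with follow-up ODI, and c that of Tampa with baseline ODI. Then R² = (ρ² + m² − 2ρmc)/(1 − c²). The SE ratio for adding Tampa to a model with baseline ODI is √[(1 − R²)/(1 − ρ²)].
- ρ = 0.5, m = 0.3, c = 0.5: √(0.747/0.75) = 0.998, almost no gain.
- ρ = 0.5, m = 0.5, c = 0: √(0.50/0.75) = 0.816, an 18 % lower SE.

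Across ρ and m of 0.3 or 0.5 and c from 0 to 0.5, the further SE reduction is about 0 to 18 %, before the cost of estimating the covariate.

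**3. Chance imbalance**

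Treating Tampa as simply randomized, the standardized difference between arms has SE √(2/20) = 0.316.
- P(at least 0.3 SD) = 2 × P(Z > 0.3/0.316) = 0.343.
- P(at least 0.5 SD) = 2 × P(Z > 0.5/0.316) = 0.114.

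These are upper values at 20 per arm, because minimizing on ODI balances Tampa in so far as the two are related. With 16 per arm analyzed (assumed), the corresponding values are 0.396 and 0.157.

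**4. What an imbalance does**

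The shift in the ODI difference is r × imbalance. At r = 0.4 and 0.5 SD (in the part of Tampa not explained by baseline ODI) it is 0.4 × 0.5 = 0.2 residual SD. That is 0.2/0.316, or about 0.6 of one standard error.

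**5. Whether the baseline tests would catch it**

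A 0.5 SD difference gives t = 0.5/0.316 = 1.58, p about 0.12 on 38 degrees of freedom. It would pass as equivalent; the tests flag only differences above about 0.64 SD.

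**The case against.** **The choice of covariates belongs in the SAP, which is not at hand.** This has some force: a one-paragraph analysis section need not list everything, and an SAP may add a covariate. But the point does not rest on silence alone. The section spells out the model's effects, and as written they leave out a predictor that the same protocol calls powerful.

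**This is a feasibility pilot.** This stands as a limit on importance. Even so, the protocol also sets out to assess efficacy, estimate treatment effects and test at 5 %.

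**The planned design already absorbs part of Tampa.** This stands. If baseline is a level of Time, which the protocol does not say, the Group x Time contrast removes whatever part of Tampa is already expressed in baseline ODI. Minimizing on ODI helps too. Hence the gain is stated given baseline ODI, and the imbalance figure as an upper value.

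**Stronger inferences that a reader might draw.**
- *The ODI comparison is biased, or its type I error inflated.* It is not: allocation keeps it unbiased on average and the unconditional error at 5 %. Only the result conditional on an actual imbalance is affected.
- *An imbalance in Tampa passes in full into the ODI result.* It passes only in proportion to the correlation that remains after baseline ODI.
- *The protocol contradicts itself by not minimizing on Tampa.* It does not: the factors were those the neurosurgeons identified, and Tampa has a stated exploratory use.
- *Pain should be adjusted for Tampa as well.* The protocol claims prediction of postoperative disability and of poor performance on physical tests, not of pain.

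**Conclusion.** The point holds as a modest, inexpensive gain in precision that the plan forgoes, and as a chance imbalance that it leaves uncorrected. It is not a flaw that invalidates the comparison.

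The size depends on a correlation that the protocol does not give. At an assumed partial correlation of 0.5 the gain is substantial for a trial of 40, at 0.3 it is small, and at 0.2 or below there is almost none. The protocol's own wording points towards the upper part of that range but supplies no figure. An imbalance large enough to matter is possible but unlikely, and the planned baseline tests would often miss it. All figures assume about 20 per arm and a comparison of single postoperative values.

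**What to change.** In the Statistical analysis section of the protocol:

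1. Prespecify the between-group analysis of ODI as a model of the postoperative values, adjusted for baseline ODI and the baseline Tampa total as a continuous covariate. Baseline ODI enters as a covariate, not as a level of Time.
2. If baseline is kept as a level of Time, include Tampa x Time. A Tampa main effect alone would leave the Group x Time contrasts essentially unchanged in complete data, because those contrasts are within patients.
3. Use only the score taken before allocation. Later Tampa scores may be affected by the training.
4. State that the baseline significance tests do not decide whether to adjust.
5. Report the same analysis without Tampa as a sensitivity analysis.
6. Limit the Tampa adjustment to ODI.

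The change needs a few sentences and no new data. It costs one degree of freedom for Tampa, or a few with Tampa x Time, and brings almost no benefit if the partial correlation is about 0.2 or less. At this sample size the covariates should be few. The choice should be fixed before results are seen, since adding Tampa afterwards would look selective.
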